## Study Population

This is a retrospective study of consecutive anaphylaxis deaths of all ages in Australia between 1^st^ January 2003 and 31^st^ December 2022.

# General Statistical Methodology

## Analysis Software

All analyses will be performed using Stata Release 19.0 or later.

## Data verification

A thorough data cleaning and data checking process of the database that will enable detection and correction of discrepancies will be conducted prior to analysis.

## Adjustment for Multiplicity

No formal adjustments for multiplicity of testing will be applied, with results interpreted based on the magnitude of the estimates and the 95% confidence intervals (CIs) rather than focussing on p-values.

## Handling of Missing Data

The analyses for all outcomes will be conducted using participants with available data.

However, if there are >10% missing data in the primary or key secondary outcomes (or exposure variables), we will conduct a sensitivity analysis under a plausible assumption regarding the missingness mechanism. Multiple imputation will be used to handle the missing data in all models used for outcomes. Imputations will be generated using chained equations, also known as fully conditional specification, with 50 imputed datasets and 10 iterations between each imputation. Any variables that are predictors of missingness and/or associated with the incomplete outcomes will be included as auxiliary variables in the imputation model. Estimates of interest will be obtained using Rubin’s rules, and will be reported with 95% confidence intervals and *p*-values.

For the analysis of time-to-event outcomes, rather than using multiple imputation, we will handle missing data (i.e. those who did not experience the outcome) by censoring those patients at the time of death.

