## Secondary Objectives

To compare the following outcomes by patient allergen exposure:

1. Time to symptoms from allergen exposure.
2. Time from symptom onset to severe symptoms.
3. Time from severe symptoms to cardiorespiratory arrest.
4. Time from arrest to death.
5. Whether the patient required tracheal intubation.
   1. If required tracheal intubation, the timing of tracheal intubation.
   2. Time to tracheal intubation from cardiorespiratory arrest.
6. Whether the patient experienced vomiting or aspiration.
7. Whether the patient received cardioversion (defined as no shocks vs at least one shock).
8. Change in posture.
9. Frequency of deaths per year over time (by allergen exposure and by age group).

To compare primary organ failure by the following complications:

1. Difficult airway (FONA, failed intubation, or 3 or more attempts at intubation)
2. FONA (front of neck access)
3. Vomiting or aspiration
4. Pneumothorax (dichotomised to none OR one+/- both sides)
5. Cardioversion

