**6.2 Sensitivity Analyses**

A sensitivity analyses will be conducted that uses multiple imputation to handle missing data if there is >10% missing data in the analysis model.

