| **Cardioversion** | NR | NR | 1.737 (0.276 to 10.948) | 0.557 | N/A | N/A |

**Table S4:** Association between complication and allergen exposure

|  | **Number (%) with complication among those with allergen exposure** | **Number (%) with complication among those without allergen exposure** | **Complete case analysis** | | **Multiple imputation** | |
| --- | --- | --- | --- | --- | --- | --- |
|  |  |  | **Odds ratio (95% CI)** | **p-value** | **Odds ratio (95% CI)** | **p-value** |
| **Allergen Exposure: Drug** | | | | | | |
| **Difficult airway** | 14/134 (10.4%) | 13/103 (12.6%) | 0.808 (0.362 to 1.803) | 0.602 | 0.931 (0.421 to 2.058) | 0.860 |
| **Cricothyroidotomy** | 5/141 (3.5%) | 7/112 (6.2%) | 0.551 (0.170 to 1.787) | 0.321 | 0.630 (0.211 to 1.880) | 0.406 |
| **Vomiting or aspiration** | 19/179 (10.6%) | 39/172 (22.7%) | 0.405 (0.223 to 0.734) | 0.003 | 0.411 (0.228 to 0.740) | 0.003 |
| **Pneumothorax** | 17/161 (10.6%) | 10/162 (6.2%) | 1.794 (0.795 to 4.049) | 0.159 | 1.857 (0.826 to 4.175) | 0.134 |
| **Cardioversion** | 34/56 (60.7%) | 17/55 (30.9%) | 3.455 (1.577 to 7.566) | 0.002 | N/A | N/A |
| **Allergen Exposure: Food** | | | | | | |
| **Difficult airway** | 6/51 (11.8%) | 21/186 (11.3%) | 1.048 (0.399 to 2.751) | 0.925 | 0.853 (0.334 to 2.177) | 0.739 |
| **Cricothyroidotomy** | NR | 10/203 (4.9%) | 0.804 (0.171 to 3.792) | 0.783 | 0.561 (0.114 to 2.764) | 0.477 |
| **Vomiting or aspiration** | 26/64 (40.6%) | 32/287 (11.1%) | 5.452 (2.934 to 10.132) | 0.000 | 5.295 (2.876 to 9.749) | 0.000 |
| **Pneumothorax** | NR | 23/264 (8.7%) | 0.762 (0.253 to 2.293) | 0.629 | 0.698 (0.235 to 2.069) | 0.516 |
| **Cardioversion** | 6/21 (28.6%) | 45/90 (50.0%) | 0.400 (0.142 to 1.124) | 0.082 | N/A | N/A |
| **Allergen Exposure: Insect** | | | | | | |
| **Difficult airway** | 5/24 (20.8%) | 22/213 (10.3%) | 2.285 (0.776 to 6.724) | 0.134 | 1.679 (0.571 to 4.938) | 0.344 |
| **Cricothyroidotomy** | 5/28 (17.9%) | 7/225 (3.1%) | 6.770 (1.988 to 23.057) | 0.002 | 5.302 (1.512 to 18.586) | 0.009 |
| **Vomiting or aspiration** | 7/63 (11.1%) | 51/288 (17.7%) | 0.581 (0.250 to 1.348) | 0.206 | 0.546 (0.236 to 1.264) | 0.158 |
| **Pneumothorax** | NR | 23/263 (8.7%) | 0.745 (0.248 to 2.241) | 0.601 | 0.756 (0.253 to 2.263) | 0.617 |
| **Cardioversion** | 3/20 (15.0%) | 48/91 (52.7%) | 0.158 (0.043 to 0.577) | 0.005 | N/A | N/A |
| **Allergen Exposure: Contrast** | | | | | | |

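### Cardioversion, the complication with the most missing data (68% in Table S4, 65% in Table S3), has no imputation result and no stated reason, so its figures describe only a third of deaths

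*Combined protocol and SAP*

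**What the plan says.** Under Handling of Missing Data, the SAP analyses available data and adds a sensitivity analysis "if there are >10% missing data in the primary or key secondary outcomes" or in exposure variables. It does not define which secondary outcomes are key. Section 6.2, which covers the secondary outcomes, drops that qualifier: the sensitivity analysis "uses multiple imputation to handle missing data if there is >10% missing data in the analysis model". The only stated exception is "For the analysis of time-to-event outcomes, rather than using multiple imputation", where censoring is used.

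Cardioversion is not a time-to-event outcome. Secondary Objectives lists it as "Whether the patient received cardioversion (defined as no shocks vs at least one shock", section 6.1 labels it binary, and it is also one of the five complications to be compared with primary organ failure.

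The drug row for cardioversion in Table S4 reads "34/56 (60.7%) | 17/55 (30.9%) | 3.455 (1.577 to 7.566) | 0.002 | N/A | N/A". The two N/A entries are the imputation columns. The same blank appears in all four cardioversion rows of Table S4 and all three of Table S3. Every other complication row has an imputation estimate except contrast with cricothyroidotomy, which has a zero cell. No reason is given for cardioversion.

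**The concern.** The planned check is absent from the complication with the fewest usable records, while pneumothorax, at 8 to 9% missing, was imputed. Under Adjustment for Multiplicity the SAP asks readers to judge results by the size of the estimates and their confidence intervals. For cardioversion, that size comes from complete cases alone.

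Two things are at stake. One is the percentages: a reader may take 60.7% as the share of fatal drug reactions in which a shock was given, when the status of most of those deaths is unknown. The other is the odds ratios, of which drug (3.455) and insect (0.158) are the most marked in the Table S4 cardioversion rows. Agreement between the two methods cannot be assumed: in Table S3, the odds ratio for difficult airway with upper airway failure falls from 6.696 to 3.401 on imputation, with far less missing.

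**Working it through.** **Denominators.** In Table S4 the vomiting/aspiration row for drug, "19/179 (10.6%) | 39/172 (22.7", gives 179 + 172 = 351. The four trigger groups in that outcome agree: 179 + 64 + 63 + 45 = 351. In Table S3 the same outcome gives 53 + 197 = 250. Neither table prints a missing count, so both totals are inferred.

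**Share without data** = 1 − (row total / largest total in the same table).

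| Complication | Table S4 | Table S3 |
| --- | --- | --- |
| Cardioversion | 1 − 111/351 = 68.4% | 1 − 87/250 = 65.2% |
| Difficult airway | 1 − 237/351 = 32.5% | 1 − 189/250 = 24.4% |
| Cricothyroidotomy | 1 − 253/351 = 27.9% | 1 − 206/250 = 17.6% |
| Pneumothorax | 1 − 323/351 = 8.0% | 1 − 227/250 = 9.2% |

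**Reproducing the printed odds ratios** (cross-product ratio, Wald interval on the log scale):

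- Drug, 34/56 v 17/55: (34 × 38)/(22 × 17) = 3.455 (1.577 to 7.566), as printed.
- Insect, 3/20 v 48/91: (3 × 43)/(17 × 48) = 0.158 (0.043 to 0.577), as printed.
- The food and contrast rows (0.400, 1.674) and the two Table S3 rows with printed counts (0.758, 1.172) also reproduce.

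**Scenario A: no unrecorded death was shocked.**

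- Drug: 34/179 = 19.0% v 17/172 = 9.9%; OR (34 × 155)/(145 × 17) = 2.14 (1.15 to 3.99), log SE 0.319.
- Insect: 3/63 v 48/288; OR (3 × 240)/(60 × 48) = 0.25 (0.08 to 0.83).

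**Scenario B: every unrecorded death was shocked.**

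- Drug: (34 + 123)/179 = 157/179 v (17 + 117)/172 = 134/172; OR (157 × 38)/(22 × 134) = 2.02 (1.14 to 3.59).
- Insect: (3 + 43)/63 = 46/63 v (48 + 197)/288 = 245/288; OR (46 × 43)/(17 × 245) = 0.475 (0.25 to 0.90).

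Overall frequency is 51/111 = 45.9% as recorded, 51/351 = 14.5% under A and 291/351 = 82.9% under B.

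**Between A and B.** The two scenarios bound the percentages but not the odds ratio. With a common shock rate of 10%, 25% or 45% among unrecorded deaths, the drug OR is 1.74, 1.54 or 1.46. At 25% the expected counts are 64.75/179 v 46.25/172; the log SE is √(1/64.75 + 1/114.25 + 1/46.25 + 1/125.75) = 0.232, so the interval is about 0.98 to 2.43 even when filled-in values are treated as observed.

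**Opposite extremes.** No unrecorded drug death shocked and all others shocked: (34 × 38)/(145 × 134) = 0.07. The reverse: (157 × 155)/(22 × 17) = 65.

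**Recording by trigger.** Drug 56/179 = 31.3%, food 21/64 = 32.8%, insect 20/63 = 31.7%, contrast 14/45 = 31.1% (chi-square p = 0.996).

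**The case against.** A reader might infer that cardioversion was recorded mainly when shocks were given, so that the complete cases are selected on the outcome and the odds ratios are biased. The documents do not support this. Of the 111 recorded deaths, 60 are negative, no base rate is given, and recording is even across triggers. Moreover, if recording depended on shock status alone, the percentages would be distorted but the odds ratio would not, as in case-control sampling. Bias in the odds ratio needs recording to depend on shock status and trigger jointly. Scenario A implies exactly that: unshocked status would have been recorded for 22/145 (15%) of drug deaths and 38/155 (25%) of the rest. But it is only a scenario.

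Some values may be structurally absent. Table 2 has yes/no items on other resuscitation and on arrhythmia or shocks, and its branching is not described. If the shock fields opened only for some deaths, imputing over all 351 would be wrong. With 68% missing, or with recording that depends on the unseen value, standard chained equations may also be unreliable. Either could justify leaving imputation out. Table 2 codes No and Not recorded separately for the shock items, so recoding one as the other cannot be the main analysis.

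These results are secondary, unadjusted and descriptive, and both intervals still exclude 1 in scenarios A and B. The main paper is not among the documents and may explain the N/A.

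All of this limits what can be said about bias. It does not supply the missing reason, the denominator or the unknown counts.

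**Conclusion.** The point holds as a departure from the stated rule and a reporting gap. Section 6.2 calls for imputation above 10% missing; cardioversion has 68% (S4) and 65% (S3) without data, no imputation result and no explanation. Its percentages and odds ratios describe only the third of deaths with a recorded status.

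In scenarios A and B the drug OR falls from 3.455 to 2.14 or 2.02, and the insect OR moves from 0.158 to 0.25 or 0.475. Direction holds in both, with a smaller association; a common intermediate rate brings the drug OR nearer to 1. Without some assumption about the missing values, direction is not identified. Selection of the recorded deaths is plausible and untested.

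This rests on 351 and 250 being the correct totals and on the unrecorded deaths belonging in the denominator. The second fails if the outcome was meant only for deaths with attempted resuscitation. The imputation estimate itself cannot be derived from the published counts. Nothing in the documents indicates that the threshold was set aside deliberately.

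**What to change.** - Define the cardioversion denominator: all deaths, or only those in which resuscitation was attempted.
- Print the number with unknown status in each trigger group, suppressing counts below five as the ethics condition requires. The insect cardioversion row in Table S4 already prints a count below five and needs the same check.
- Apply the section 6.2 rule to cardioversion, or state why imputation is unsuitable.
- Beside each complete-case result, report the none-shocked and all-shocked scenarios on the defined denominator. Add at least one intermediate rate, because the two scenarios do not bracket the odds ratio.
- Describe the recorded percentages as applying to deaths with known status.

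The cost is a few extra tabulations and models on data already held. The price in presentation is a weaker drug and insect association than the complete-case rows show.

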# Descriptive Statistics

## Baseline Characteristics

The following variables will be summarised at baseline. Categorical variables will be summarised as the number and percentage, and continuous variables as mean, standard deviation (SD) and range.

**Baseline variables:**

- Sex
- Age (continuous)
- Age (categorical): 0-4, 5-17, 18-39, 40-59 and >60 years
- Pre-existing asthma/COPD status
- Pre-existing anti-hypertensive documented
- ASA score
- Any known allergies
- Known allergy to trigger
- Location of allergen exposure

# Analysis of the Primary Outcome

## Primary Analysis

*Causal effect of allergen exposure trigger on primary organ failure*

The analysis will include allergen trigger as the exposure variable of interest and primary organ failure (defined as whether the primary organ failure was upper airway, bronchospasm, or cardiovascular) as the outcome in three models (where each type of organ failure is a separate outcome). We will fit a logistic regression model, adjusted for the set of confounders listed below, and estimate an adjusted odds ratio reported with its 95% confidence interval (CI) and p-value. If we identify effect modifiers, an adjusted marginal odds ratio will be reported, estimated following model fitting using g-computation. We will also report the number and percentage meeting the outcome in each exposure group. Since the exposure variable has multiple categories, we will present each pairwise odds ratio.

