Count outcomes will be summarised by exposure group for each time point (i.e. reporting the number of deaths in each year by exposure). The adjusted incidence rate ratio will be estimated using Poisson regression, reported with the 95% CI and p-value. Given that we suspect that the rate of death is not constant over time, an exposure x time interaction term will be included in the model. If there is evidence of non-constant rate over time, we will present the marginal adjusted incidence rate ratio. If there is any evidence of overdispersion, we will instead use negative binomial regression to estimate the incidence rate ratios.

Nominal outcomes will be compared between exposure group by using cross-tabulations. If there are >5 expected counts in each cell, we will use the Chi-Square test as a measure of association.

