| **Insect** | 21/37 (56.8%) |  |  |  |  |
| **Food** | 0/58 (0.0%) |  |  |  |  |
| **Contrast** | 12/27 (44.4%) |  |  |  |  |
| **Adjusted estimates (causal effects)** | | | | | |
| **Insect v Drug** | - | 2.920 (1.208 to 7.055) | 0.018 | 3.076 (1.296 to 7.305) | 0.011 |
| **Food v Drug** | - | Cannot be estimated | N/A | Cannot be estimated | N/A |
| **Contrast v Drug** | - | 1.589 (0.668 to 3.781) | 0.293 | 1.503 (0.612 to 3.691) | 0.371 |
| **Food v Insect** | - | Cannot be estimated | N/A | Cannot be estimated | N/A |
| **Contrast v Insect** | - | 0.544 (0.178 to 1.667) | 0.285 | 0.489 (0.157 to 1.516) | 0.213 |
| **Contrast v Food** | - | Cannot be estimated | N/A | Cannot be estimated | N/A |
| **Unadjusted estimates (associations)** | | | | | |
| **Insect v Drug** | - | 2.461 (1.156 to 5.237) | 0.019 | 2.591 (1.238 to 5.422) | 0.012 |
| **Food v Drug** | - | Cannot be estimated | N/A | Cannot be estimated | N/A |
| **Contrast v Drug** | - | 1.500 (0.641 to 3.511) | 0.350 | 1.535 (0.646 to 3.648) | 0.331 |
| **Food v Insect** | - | Cannot be estimated | N/A | Cannot be estimated | N/A |
| **Contrast v Insect** | - | 0.610 (0.224 to 1.656) | 0.332 | 0.592 (0.212 to 1.655) | 0.316 |
| **Contrast v Food** | - | Cannot be estimated | N/A | Cannot be estimated | N/A |

**Table S2c**: Summary of overall average causal effect of allergen exposure on primary organ failure (Upper airway)

| **Exposure or Contrast** | **Number (%) with upper airway as primary organ failure** | **Complete case analysis** | | **Multiple imputation** | |
| --- | --- | --- | --- | --- | --- |
|  |  | **Odds ratio (95% CI)** | **p-value** | **Odds ratio (95% CI)** | **p-value** |
| **Drug** | 7/115 (6.1%) |  |  |  |  |
| **Insect** | 7/37 (18.9%) |  |  |  |  |
| **Food** | NR |  |  |  |  |
| **Contrast** | NR |  |  |  |  |
| **Adjusted estimates (causal effects)** | | | | | |
| **Insect v Drug** | - | 3.534 (0.927 to 13.468) | 0.064 | 3.610 (1.186 to 10.991) | 0.024 |
| **Food v Drug** | - | 2.946 (0.393 to 22.082) | 0.292 | 2.113 (0.277 to 16.150) | 0.468 |
| **Contrast v Drug** | - | 6.935 (2.183 to 22.032) | 0.001 | 2.565 (0.566 to 11.621) | 0.220 |
| **Food v Insect** | - | 0.834 (0.127 to 5.486) | 0.849 | 0.585 (0.079 to 4.343) | 0.598 |
| **Contrast v Insect** | - | 1.962 (0.560 to 6.881) | 0.291 | 0.711 (0.131 to 3.844) | 0.690 |
| **Contrast v Food** | - | 2.354 (0.329 to 16.828) | 0.392 | 1.214 (0.098 to 15.087) | 0.879 |

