| **Unadjusted estimates (associations)** | | | | | |
| **Insect v Drug** | - | 3.600 (1.171 to 11.067) | 0.025 | 3.083 (1.129 to 8.416) | 0.028 |
| **Food v Drug** | - | 0.842 (0.209 to 3.382) | 0.808 | 0.632 (0.156 to 2.566) | 0.520 |
| **Contrast v Drug** | - | 1.234 (0.242 to 6.303) | 0.800 | 1.494 (0.317 to 7.041) | 0.610 |
| **Food v Insect** | - | 0.234 (0.056 to 0.971) | 0.045 | 0.205 (0.050 to 0.847) | 0.029 |
| **Contrast v Insect** | - | 0.343 (0.065 to 1.801) | 0.206 | 0.485 (0.098 to 2.387) | 0.371 |
| **Contrast v Food** | - | 1.467 (0.230 to 9.333) | 0.685 | 2.363 (0.379 to 14.722) | 0.356 |

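### The primary logistic models have no plan for zero or sparse cells: half the cardiovascular contrasts have no estimate, and one adjusted upper-airway odds ratio is unstable

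*Combined protocol and SAP*

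**What the plan says.** The SAP (Analysis of the Primary Outcome, Primary Analysis) treats upper airway, bronchospasm and cardiovascular failure as separate binary outcomes. For each, "We will fit a logistic regression model, adjusted for the set of confounders listed below, and estimate an adjusted odds ratio". The only listed confounder is age. Four potential effect modifiers are listed (age, asthma/COPD, antihypertensive use, ASA score), with this rule: "If we identify effect modifiers, an adjusted marginal odds ratio will be reported, estimated following model fitting using g-computation". The output is promised in full: "Since the exposure variable has multiple categories, we will present each pairwise odds ratio".

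The primary models have no rule for empty or sparse cells. The only expected-count rule is in section 6.1, for nominal secondary outcomes: "If there are >5 expected counts in each cell, we will use the Chi-Square test as a measure of association".

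In Table S2b each contrast involving Food reads "Cannot be estimated | N/A | Cannot be estimated | N/A", in both the adjusted and the unadjusted block. In Table S2c the adjusted Contrast v Drug odds ratio is 6.935 (2.183 to 22.032), p=0.001, for complete cases and 2.565 (0.566 to 11.621), p=0.220, after imputation. The unadjusted complete-case value is 1.234 (0.242 to 6.303), p=0.800. The sentence introducing these tables tells the reader that the two analyses hardly differ in strength or significance.

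**The concern.** Maximum-likelihood logistic regression has no finite solution for a group with no events. Very uneven cells were foreseeable: the protocol's background describes food deaths as predominantly respiratory and gives 59% to 81% cardiovascular collapse in venom series. A plan that promises every pairwise odds ratio therefore needed a method for this case. Without one, three contrasts on the primary question have no estimate and no confidence limit.

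The upper-airway model raises a different problem. It can be fitted, but with few events its adjusted results may depend heavily on which terms are included. One row, presented as a causal effect with p=0.001, has no counterpart in the crude or imputed analysis. A reader could take it as evidence that contrast favours upper-airway failure.

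**Working it through.** **1. Inputs and reproduction of the published figures.** Counts are from Tables S2a to S2c. Cells marked * are withheld there and obtained by subtraction.

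| | Drug | Insect | Food | Contrast | Total |
|---|---|---|---|---|---|
| Deaths analysed | 115 | 37 | 58 | 27 | 237 |
| Bronchospasm | 68 | 9 | 55 | 13 | 145 |
| Cardiovascular | 40 | 21 | 0 | 12 | 73 |
| Upper airway | 7 | 7 | 3* | 2* | 19 |

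Subtraction: Food 58−55−0=3; Contrast 27−13−12=2. This needs the three types to exhaust each denominator, which Drug (68+40+7=115) and Insect (9+21+7=37) confirm. The derived counts also return the published crude odds ratios: Contrast v Drug (2×108)/(25×7)=1.234; Food v Drug (3×108)/(55×7)=0.842. All 15 estimable crude complete-case odds ratios in the three tables reproduce to three decimals, with intervals agreeing to rounding.

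**2. The zero cell.** Food v Drug for cardiovascular failure is (0×75)/(58×40)=0, so the log odds ratio is minus infinity. The same holds for every contrast with Food: 3 of 6.

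With trigger as the only term, the Firth point estimate equals adding 0.5 to each cell:

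- Food v Drug: (0.5×75.5)/(58.5×40.5)=0.016; profile-likelihood 95% CI 0.0001 to 0.116; exact upper limit 0.133.
- Food v Insect: (0.5×16.5)/(58.5×21.5)=0.0066; CI 0.00005 to 0.052; exact upper limit 0.063.
- Contrast v Food: (12.5×58.5)/(15.5×0.5)=94.4; CI 11.3 to 12,340; exact lower limit 9.1.

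The crude Food v Drug risk difference is 0−34.8=−34.8 points (Newcombe 95% CI −43.9 to −24.6).

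**3. Precision of the upper-airway rows.** The standard error implied by a published interval is ln(upper/lower)/3.92.

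- Contrast v Drug, adjusted complete case: ln(22.032/2.183)/3.92=0.590; z=ln(6.935)/0.590=3.28; p=0.001. The p-value agrees with its interval.
- Contrast v Drug, crude: ln(6.303/0.242)/3.92=0.832, matching √(1/2+1/25+1/7+1/108)=0.832.
- Contrast v Drug, adjusted and imputed: ln(11.621/0.566)/3.92=0.771.
- Insect v Drug: 0.573 crude, 0.683 adjusted.
- Food v Drug: 0.710 crude, 1.028 adjusted.

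Against Drug, adjustment widened the intervals for Insect and Food but narrowed the one for Contrast, the group with fewest events. The result, 0.590, is below √(1/2)=0.707, the contribution of the two Contrast events alone to the crude standard error. Firth on the crude counts gives 1.42 (0.25 to 5.71), p=0.66.

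**4. Where the narrow interval might come from.** With three trigger terms and one age term there are 19/4=4.8 events per coefficient; with age-by-trigger interactions, 19/7=2.7. An illustrative simulation kept the observed counts, assumed mean ages of 58, 52, 25 and 64 (Drug, Insect, Food, Contrast), and assigned events at random within trigger.

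| Standardised Contrast v Drug odds ratio | SE, 5th to 95th percentile | p<0.05 | OR>6 and p<0.01 |
|---|---|---|---|
| Age as main effect (1000 runs) | 0.82 to 0.85 | 0% | 0% |
| Age-by-trigger interaction (996 usable runs) | 0.62 to 1.68 | 8.4% | 5.3% |

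Only the interaction model with g-computation produced rows like the published one. The ages are assumptions.

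**The case against.** Much of the opposing case stands.

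- **Fit of the upper-airway model.** A reader might infer that ordinary logistic regression cannot handle these cells. It can: all six crude odds ratios are finite and reproduce. Only the true zero is unfittable.
- **Cause of p=0.001.** A reader might infer that sparse-data maximum likelihood is shown to be responsible. It is not. The documents state neither the fitted terms nor the number of cases in the adjusted model. The title of Table S2c refers to an overall average causal effect, which suits a standardised odds ratio, and crude standard errors are not strict lower bounds for that quantity. Interaction plus g-computation is the likeliest explanation, by inference only.
- **What was lost.** A reader might take 0.016 as the missing primary estimate. It is crude, while the plan adjusts for age. For bronchospasm, Food v Drug falls from 12.672 crude to 1.980 adjusted, so the gap may be large. The penalty also largely sets the point estimate when a cell is zero. The counts 0/58, 40/115, 21/37 and 12/27 are published, so the pattern is visible; what is missing is an effect estimate and its limits.
- **Disclosure.** The imputed value is in the same row and the crude value in the same table, and the SAP asks readers to weigh estimates and intervals over p-values. That lessens the risk of misreading, but the introductory sentence about the tables works the other way.

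**Conclusion.** The SAP lacks a sparse-data method for its primary models. As a direct result, 3 of 6 cardiovascular contrasts have no estimate, adjusted or unadjusted, complete-case or imputed. A standard penalised method would have given finite results. The crude figures above show that this is feasible; they do not give the age-adjusted answer, because individual ages are not in the documents.

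Separately, the adjusted complete-case upper-airway Contrast v Drug result is unstable and should not be relied on. It rests on two Contrast events, derived by subtraction, and neither its size nor its significance survives in the crude or imputed analysis. It also contradicts the statement that the two analyses hardly differ. The cause remains inferred until the fitted model is stated.

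Two stronger conclusions are not supported. Bronchospasm has 145 events in 237 deaths and no zero cell, so its estimator does not need replacing. Nor should the 6.935 result be withdrawn: available-case analysis was prespecified, and removing a planned result after seeing it would be selective reporting.

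**What to change.** 1. Use age-adjusted Firth penalised logistic regression for any primary model with a zero or sparse cell, here cardiovascular and upper airway. Leave bronchospasm as planned. Label this as added after the data were seen.
2. Report profile-likelihood intervals for complete cases. State how the imputed results are pooled, because these intervals do not combine directly under Rubin's rules, which the SAP's missing-data section requires.
3. Fit upper airway with main effects only, without modifier interactions. Firth alone would not cure instability that comes from interaction terms.
4. Limit any g-computation to ages observed in both groups being compared.
5. Report risk differences beside the odds ratios, labelled as unadjusted where they are.
6. Re-estimate the 6.935 result, state the model and number of cases behind it, and keep it in the table flagged as unreliable.
7. Correct the sentence introducing Tables S2a to S2c.

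The cost is SAP wording, a re-run on existing data and some extra work on pooling. The statistical price is slight shrinkage and very wide intervals for the Food cardiovascular contrasts.
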